### Research hypotheses

Our primary research question is to understand the potential impacts of GI on BEAs investment in their future (education, employment, training), mental health (depressive symptoms), and unmet mental health (MH) and sexual/reproductive health (SRH) service needs. We are also interested in learning if complementary financial supports propel greater impact on health outcomes and understanding to what degree GI impacts dissipate after the transfers end. Thus, our hypotheses are as follows.

*H1*: *GI will improve all outcomes*. Youth receiving GI in phase I will have greater increases in investments in their future (H_1a_), greater decreases in depressive symptoms (H_1b_), and larger reductions in unmet need for MH and SRH services (H_1c_) at 12 months than those who do not received GI in phase I.

*H2*: *GI + financial supports will improve outcomes more than GI alone*. Participants receiving GI in phase I who participate in mentoring or peer discussion groups will have greater increases in investments in their future (H_1a_), greater decreases in depressive symptoms (H_1b_), and larger reductions in unmet need for MH and SRH services (H_1c_) at 12 months than those not opting into financial support programs.

*H3*: *Gains from GI will be sustained*. Participants receiving GI in phase I will not experience a decline in odds of enrollment in educational/training programs (H_3a_) or an increase in odds of depressive symptoms (H_3b_) or unmet need for MH and SRH services (H_3c_) following the removal of GI (between month 12 and 24).

*H4*: *Accessing complementary financial supports prior to receiving GI will improve overall outcomes.* Among BEA who do not receive GI in phase I, those who engage in mentoring or peer discussion groups in phase I will have greater increases in investments in their future (H_4a_), greater decreases in depressive symptoms (H_4b_), and larger reductions in unmet need for MH and SRH services (H_4c_) at 24 months than BEA who did not opt-in into the financial programming prior to receiving GI.

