### Data collection and assessments

#### Structured surveys

We conduct comprehensive surveys annually and brief monitoring surveys of primary outcomes every 3 months, with some additional secondary outcomes and covariates collected at six-month intervals. Annual comprehensive surveys are conducted in-person at enrollment, 1 year (point of cross-over) and 2 years. The annual survey will assess primary and secondary outcomes as well as covariates. Brief 3-month surveys are completed online and focus on primary outcomes and any change in demographics, such as living situation. Links for the brief 3-month surveys are sent by SMS or email, depending on participant preference, up to four times within a 10-day window, with a final personalized reminder sent 1 day before the link expires. All surveys–both comprehensive and brief–are collected in REDCap by CAPI (Computer-assisted personal interviewing) in order to ensure privacy and consistency in data collection. Soft credit checks require an additional consent and are performed to assess participants’ baseline credit scores, following enrollment, and again at 6 and 12 months. Participants are remunerated for all surveys via their preferred form of payment (CashApp or gift card). Centering BEA needs and preferences, payment options were determined in consultation with BEA and the CWG.

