#### Sample size estimation

Power analyzes were generated using the equation defined by Diggle et al. (97) to compute minimum detectable effect sizes for the primary analyses to address Hypotheses 1a-1c. The study will begin with 300 participants equally allocated to two study groups. Assuming 25% attrition over 12 months, we anticipate an average of 4.3 observations from 300 participants will be available for analysis of investments in the future and mental health outcomes and an average of 5.7 observations for analysis of unmet service need outcomes. Assuming *α* = 0.05 and power = 0.80, with four highly correlated post-baseline measurements [intraclass correlation (ICC) = 0.20–0.80] and a range of outcomes for waitlist control participants (change in each outcome between 5 and 40%), we will have sufficient power to detect differences as low as 5.7–10.7% for increase in enrollment in educational or training programs and decrease in depression, and 4.5–10.6% for decrease in unmet service need, respectively, in the intervention arm compared to waitlist controls.

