#### Secondary analyses

We will determine if BEA receiving GI in Phase 1 who opt-in to peer discussion groups and financial mentoring will have larger increases in odds of investment in the future, larger declines in odds of depressive symptoms and larger declines in odds of unmet mental and sexual health service needs at 12 months compared to those who did not opt into these support programs (H2). We will use the same modeling approach as described above for H1 used to test H2 except that analysis will be restricted to a single arm of the study (those receiving GI in phase I or those receiving GI in phase II).

As in our preliminary analyses, we will employ causal inference methods to adjust for any differences between sub-strata [e.g., individuals who do or do not opt in to financial mentoring or peer discussion groups at baseline or due to differential loss to follow-up]. As in our primary analyses, we will use logistic GEE to model our dichotomous outcomes, and continuous GEE specifications for continuous measures. We will test H2 via DID comparison of post-baseline measurements in the Phase 1 GI group during Phase 1 (as in H1). All comparisons for secondary analyses (H2 through H4) will be tested at *α* = 0.05 per comparison.

We will test (H3)–BEA receiving GI in Phase 1 will not experience a significant decline in odds of enrollment in educational or training programs, a significant increase in odds of depression or a significant increase in odds of unmet mental and sexual health service needs following removal of the GI (between month 12 and 24)–using an interrupted time series (ITS) approach. For these ITS analyses, we will include indicators for phase, time and the interaction between phase and time to examine the slope in each outcome during Phase 1, the presence of an immediate change in each outcome after removal of GI (level effect), as well the change in slope for each outcome during Phase 2 (slope). If changes in outcomes do not follow a linear trend, we will explore alternative relationships including polynomial and spline terms.

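### The interrupted time series for H3 names no contrast that matches H3: its change-in-slope term can show a fully held gain as decline, and its level and slope terms carry the survey-mode pattern

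*Protocol article*

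**What the plan says.** Under Research hypotheses, H3 states that gains in the Phase 1 GI arm will be sustained: no fall in the odds of enrolment in education or training, and no rise in the odds of depressive symptoms or unmet service need, "following the removal of GI (between month 12 and 24". Secondary analyses repeats this target and specifies the model: "we will include indicators for phase, time and the interaction between phase and time". The quantities to be examined are the Phase 1 slope and "an immediate change in each outcome after removal of GI (level effect), as well the change in slope for each outcome during Phase 2". Polynomial or spline terms may be explored if trends are not linear. No comparison arm enters this analysis. On the error rate, the section says "All comparisons for secondary analyses (H2 through H4) will be tested at" 0.05 per comparison.

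On survey mode, Structured surveys says "Annual comprehensive surveys are conducted in-person at enrollment, 1 year (point of cross-over) and 2 years", while "Brief 3-month surveys are completed online and focus on primary outcomes". It also says that both kinds of survey are "collected in REDCap by CAPI (Computer-assisted personal interviewing", for privacy and consistency. The Discussion concedes that the H3 analysis is open to time shocks outside the study's control. It does not mention survey mode.

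**The concern.** H3 is a statement about what happens after payments stop. The change in slope is a different quantity: the Phase 2 slope minus the Phase 1 slope. If GI works gradually, the Phase 1 slope is favourable, and simply holding the gain makes the change in slope unfavourable. The better H1 succeeds in this way, the more the term looks like loss. A decline that runs unchanged through both phases gives a change in slope of zero, so the term can also miss real worsening.

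The second issue is timing. The last survey under GI (month 12) is in person and the next three (months 15, 18 and 21) are online. With no concurrent arm in the model, any difference in reporting between the two modes falls at the interruption and cannot be told apart from an effect of ending GI.

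Sustained impact is one of the trial's stated aims, so the conclusion that H3 can support matters even though it is secondary.

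**Working it through.** The article gives no margin, power or sample size for H3, so there is no H3 figure to reproduce.

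**Inputs from the article.** Quarterly points at months 0, 3, ..., 24; in person at 0, 12 and 24. "300 participants equally allocated to two study groups", so 150 in the Phase 1 GI arm. Attrition of 25% over 12 months, giving 150 × 0.75 = 112.5, taken as 112. ICC 0.20 to 0.80. Alpha 0.05, taken as two-sided. The gain G = 10.7 points is the top of the detectable range for enrolment and depression in Sample size estimation. That is a between-arm figure, used here only as a scale.

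**Assumptions not in the article.** Outcome rate 0.45; a linear build-up of the gain; 112 participants complete to month 24; the size and sign of M.

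**Model.** With t in years and phase = 1 after month 12: E(Y) = b0 + b1·t + b2·phase + b3·phase·(t − 1). Then b2 is the level change, b3 the change in slope, b1 + b3 the Phase 2 slope, and b1 + b2 + b3 the modelled month 24 minus month 12 difference.

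**Step 1: known patterns projected onto this model by least squares.**

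| True pattern | b1 | Level b2 | Slope change b3 | Phase 2 slope | 24 v 12 |
|---|---|---|---|---|---|
| Linear gain G, fully held | G | 0 | −G | 0 | 0 |
| Linear gain G, fully lost | G | 0 | −2G | −G | −G |
| Decline G per year throughout | −G | 0 | 0 | −G | −G |
| Step gain G by month 3, held, baseline included | 0.8G | −0.2G | −0.8G | 0 | −0.2G |
| Same step, baseline excluded | 0 | 0 | 0 | 0 | 0 |
| Flat truth, in-person minus online = M | 0 | −0.9M | +1.2M | +1.2M | +0.3M |
| Same, baseline excluded | 1.2M | −1.2M | 0 | +1.2M | 0 |

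For depression and unmet need, where improvement is a fall, the signs of the gain rows reverse.

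**Step 2: how often a held gain is flagged by b3.** Covariance of the estimates = (X′Σ⁻¹X)⁻¹/112, with Σ = 0.45 × 0.55 × [(1 − ICC)I + ICC·J]. The standard errors of b3 are 9.2, 7.3 and 4.6 points per year at ICC 0.2, 0.5 and 0.8. With z = 10.7/SE = 1.16, 1.47 and 2.32, the chance of significance is Φ(z − 1.96) + Φ(−z − 1.96) = 21%, 31% and 64%.

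A logistic GEE simulation is closer to the planned model. It used 150 participants, 25% dropout in each year, sandwich errors, correlation applied on a latent scale and 2000 runs per setting. For a held linear rise from 30% to 40.7%, b3 was significantly negative in 20% to 33% of runs. The Phase 2 slope and the 24 versus 12 contrast were each significantly negative in about 2% of runs, against a nominal 2.5%.

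**Step 3: size of the mode bias.** The standard error of the level term is 6.1 to 3.0 points over ICC 0.2 to 0.8.
- M = 2: false level change 0.9 × 2 = 1.8 points; rejection 6% to 9% against a nominal 5%.
- M = 10: false level change 9 points.
- In the simulation, with a true rate of 30% and in-person reports lower by 5 points, the level term was falsely significant upward in 10% to 16% of runs. At 10 points lower it was 28% to 49%. The nominal rate is 2.5%.

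The Phase 2 slope is not immune: at 10 points lower it was falsely negative in 31% to 52% of runs. A mode indicator is estimable (design rank 5 of 5, variance inflation 1.33). With it, every term returned to about 2% to 3% per tail.

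**The case against.** The strongest reply is that the article states the H3 target correctly and only says which quantities will be examined. A reader might infer that the plan tests the wrong contrast, or that H3 will be rejected whenever gains are held. The text does not support that. It never says that the change in slope alone decides H3. The Phase 2 slope is the sum of two quantities in the same fit, and the level term is relevant to an immediate loss. This part of the reply stands. What remains is that the article goes beyond naming a method: it lists the quantities to be read, omits those that match H3, and leaves open which one decides.

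The size of the slope problem depends on the path of the gain. A step gain with baseline excluded produces none. The 21% to 64% rests on a linear path, an assumed rate and month-12 retention carried to month 24. That also stands.

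On mode, a reader might infer that the level term simply measures the switch from in-person to online. It does not: three of the five Phase 1 points are online too, and no mode effect is documented. Use of the same REDCap CAPI system may reduce any difference, and for enrolment in education there is little evident reason to expect one. For the two unmet-need outcomes, if monthly check-ins enter the series as further points that are not in person, the same projection on monthly points gives about −0.32M for level and +0.46M per year for slope change, roughly a third.

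The spline option does not say which contrast is read. The Discussion's caveat covers external shocks, not a mode schedule that the study itself sets.

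**Conclusion.** The point holds in limited form. The H3 analysis lists no contrast equal to H3. If the change in slope is read as the test, a gradually built and fully held gain appears as a decline of the full gain per year, significant in about 21% to 64% of trials under the stated assumptions (20% to 33% in the logistic simulation). A decline continuing through both phases appears as no change. The problem needs a non-zero fitted Phase 1 slope.

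Survey mode is a separate and conditional weakness: about −0.9M on level (−1.2M without baseline) and +1.2M per year on slope change (0 without baseline). M is not given in the documents. The effect is small at about 2 points and material only nearer 10, and it may be smaller for unmet need. The documents do not show that a mode effect exists. They show that this model could not separate one from the removal of GI. As H3 is secondary and the remedy is simple, this should be corrected before the month-24 analysis.

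**What to change.** Within the same GEE model, name as the H3 tests (a) the model-based month 24 versus month 12 contrast, that is the level change plus 12 months of the Phase 2 slope, and (b) the Phase 2 slope, time plus phase × time. Keep the level term for immediate loss, which a month 24 versus 12 comparison would miss if it recovered. Include an in-person/online indicator as a fixed covariate, because without it the Phase 2 slope still carries +1.2M per year.

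Report the direct month 24 versus month 12 comparison, both in person, as a sensitivity check. It is free of mode and of trend misfit, such as the −0.2G that the modelled contrast shows for a held step gain with baseline included. It should not be the main test: it discards months 15 to 21, and its standard error is about 24% larger than that of the modelled contrast (at ICC 0.5, 4.70 against 3.79 points).

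The cost is some wording, one covariate and slightly wider standard errors. At ICC 0.5, adding the mode column to the covariance formula above moves the 24 versus 12 standard error from 3.79 to 3.88 points, the level term from 4.8 to 5.4, and the Phase 2 slope from 5.9 to 6.8 points per year. No new data are needed.

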#### Exploratory mediation and moderation analyses

We will conduct a number of exploratory mediation and moderation analyses. For example, in mediation analyses we will investigate whether covariates, such as food insecurity, or interim financial well-being outcomes, such as debt, credit, or income, measured at 3, 6, and 9 months mediate the relationship between intervention assignment and subsequent mental health outcomes (i.e., less anxiety and depressive symptoms) measured at 6, 9, and 12 months. We will also investigate whether changes in financial and mental health outcomes mediate the relationship between intervention assignment (GI) and reduced unmet service needs. Finally, we will explore whether intervention impacts are different by gender, parenting status, or living situation (moderation).

### Qualitative data analysis

Using thematic analysis to guide the process, the team will develop a codebook based on deductive themes (98), based on topics captured within the interview guides such as current living situation, financial aspirations, community involvement, and goals related to GI support and inductive themes, which emerge within the data. A preliminary codebook will be developed, and then the team, consisting of the interviewers, MyPath staff, and a senior investigator, will select 3–5 transcripts to code together, refining the codebook through discussion, and developing definitions and rules around code application. Coder agreement will be assessed by having each member code a portion of a transcript, comparing the total number of segments coded to the number of coded segments where analysts agreed on code application to ensure that the analysts achieve a coder agreement threshold of 90 percent. Analysis team members will discuss any discrepancies in coding approaches to resolve differences and will repeat the process to build coder agreement until the threshold is met. Once the threshold has been achieved, the transcripts will be entered into Dedoose, an online qualitative data analysis program, and the remainder of the data will be coded. This process will be repeated with every wave of data collection, as the codebook is further refined with each iteration of the interviews.

### Dissemination

Overall findings will be disseminated to the local community, including study participants and their families and communities, via dissemination meetings. Dissemination will occur first following baseline data collection, including descriptive analysis to understand the context and circumstances of our participants, next after the end of Phase 1 (H1 and H2) to report primary trial outcomes, and again following Phase 2 (H3 and H4) as results from the secondary trial outcomes become available. Dissemination to the scientific, programmatic, and policy research communities will include presentations at scientific meetings, publications in peer-reviewed journals, and fact sheets for policymakers.

### Anti-racist approaches to implementation

Historical exploitation of Black communities in medical research requires centering anti-racism in public health research, including challenging institutional norms and policies. We utilized many additional strategies to prioritize equity and center the needs of BEA through the study’s implementation. To maximize investments in the participants themselves and ensure that academic institutions do not unfairly profit from work to benefit communities of color, the BEEM project requested a waiver of institutional overhead costs associated with GI payments, which we successfully obtained from the university. Other anti-racist efforts employed by the project also required institutional change, such as advocating for and pursuing options to provide participant incentives for survey completion in the form they preferred (e.g., CashApp), which was not initially endorsed by institutional policy, but was permitted as a pilot program. The project has also maintained a very active CWG and compensates the members of our CWG for their valuable time and input. We also seek to minimize harms to participants by preventing loss of social service benefits and loss of GI payment in the form of taxed income. We consulted legal experts to successfully establish the legal basis for classifying GI as a gift and not taxable income. We have also secured state waivers to protect benefits such as CalFresh and CalWorks and included free provision of benefits counseling to all participants to address concerns about losing other benefits due to receipt of GI.

## Discussion

The BEEM Project addresses the important impact of decades of structural racism and inequitable access to opportunity and wealth generation for BEA, while also addressing scientific knowledge gaps regarding the impacts of GI on financial well-being and health outcomes. The randomized controlled crossover design supports the ability to draw causal inferences while ensuring all participants have access to no-strings-attached cash payments. This study will illuminate the impacts of complementary financial capability programming (i.e., mentoring, peer discussion groups) and their ability to bolster the effects of GI as an accompanying policy program. The extended data collection period will aid understanding of sustained impacts of GI one-year after payments end, filling a critical gap in knowledge on the degree to which the impacts of GI dissipate (follow-up for most GI projects have rarely extended beyond a few months). Results about the extended impact of GI can also provide evidence about augmenting health trajectories over the life course.

Importantly, results of the study will also help determine the utility of GI as a strategy to tackle racial health disparities. The focus of our project is on empowering low-income BEA, a group that has been made vulnerable by a history of intersecting social, economic, and political systems that result in lasting economic inequities and denied opportunities. This study will provide evidence about targeting GI within a group whose financial vulnerability and health inequalities have been created by structural racism and impact health transitions to adulthood. We apply anti-racism praxis and actively engage with communities, an approach vital for informing our approaches to affirming the autonomy of BEA, allocating and distributing resources, and challenging institutional (including research) norms.

This study has some limitations. Little is known about the unintended consequences of GI among emerging adults, but we are gathering information, such as social harms, to shed light on potential limitations of GI. The BEEM Project uses residence in low-income census tracts (or marginal housing status) as a proxy for low-income status since many young people do not know their household’s income. This may result in greater heterogeneity in baseline income levels than directly measurement of household income. However, we will assess other indicators of income and socioeconomic status (receipt of public benefits, maternal education, income earned) and can adjust for baseline differences if treatment arms are imbalanced. Selection bias may be introduced due to self-selection into the non-GI intervention components (financial mentoring and peer discussion groups). We will adjust for these differences across sub-strata in our analysis by using causal inference methods. The ITS analysis of H3 will be subject to the usual threats if other time shocks occur, such as changes in local social determinants of health outside of study control; these conditions will be monitored to assist in results interpretation. Because this study is set in two cities in California, findings may not be generalizable outside of urban areas in California. Finally, the temporary one-year nature of our GI intervention may result in smaller effects than would an ongoing GI program supporting BEA throughout their entire emerging adulthood period from age 18 to 24.

Acknowledging that structural racism drives racial health disparities, this study focuses on GI as a strategy to address the *effects* of structural racism on individuals’ health outcomes, rather than intervening on structures or institutions that perpetuate racial inequities. More investigation is needed to understand how GI may influence individuals’ interactions with structural factors. For example, it is plausible that this intervention could impact communities or policy change, especially since GI receipt has been associated with greater perceived ability to influence social change (99). Future research could examine GI recipients’ involvement with broader structural change or investigate spillover effects at neighborhood, institutional, or policy levels. On the other hand, given that structural racism has also shaped neighborhood environments via systematic disinvestment, it is also plausible that contextual neighborhood effects may potentially augment the impact of GI via resources or social capital. Future research should assess heterogeneity of treatment effects to discern whether certain contextual factors can be targeted for intervention.

